### Data analysis

Data will be analysed according to the intention to treat principle. Difference in birth weight will be assessed using parametric testing. PUQE-24 score will be analysed using multivariate regression and repeated measurements ANOVA or mixed models, as will be quality of life assessments. Other secondary outcomes will be addressed in a similar manner. For non-normally distributed variables non-parametric equivalents will be used. To evaluate the potential of each of the strategies, we will also perform a per protocol analysis, taking into account only those women that were treated according to protocol.

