**Fig. 1 Fig1:**
[figure not shown]
CONSORT 2010 flow diagram MOTHER trial

Randomisation is performed by a web based computerised program using permuted-block randomisation. Randomisation is allocated in a 1:1 ratio for standard care or enteral tube feeding in addition to standard care, with a block size of four. Stratification according to centre is applied.

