To evaluate potential HG and birth weight predictors, detailed information on obstetric and medical history, anthropometrics (before and during pregnancy), antiemetic medication use, given treatment(s) (including intravenous and/or tube feeding regimen and tube location), laboratory results, treatment and pregnancy complications and birth outcomes are collected using a standardised Case Report Form (CRF; see Additional file 1). Research staff obtains the information needed based on medical and dietician records. Maternal demographics (ethnicity, education level, marital status), mode of conception and onset of nausea and vomiting symptoms are enquired via the questionnaire.

All participants in this trial are asked for informed consent of storage of maternal blood (taken with routine laboratory analysis during hospital admission for HG), cord blood and placental biopsies (taken at birth) in an obstetrical biobank (the Preeclampsia and Non-preeclampsia Database, Academic Medical Centre Amsterdam, the Netherlands). The addition of these samples will enable molecular studies in HG aetiology and consequences. Furthermore, cord blood will be used for the assessment of plasma lipids (cholesterol, HDL, LDL, triglycerides, Apolipoprotein A and B), glucose, leptin and thyroid function (TSH, fT4).

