## Outcome measures

### Primary outcome measure

The primary outcome will be neonatal birth weight.

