## Statistical issues

### Sample size

The sample size is based on a difference in mean birth weight of 200 g (SD 400 g) between the intervention group and the control group, which we consider clinically relevant. With a beta of 0.2 and alpha of 0.05 and a possible 10 % loss to follow up, we need to randomise 120 participants (60 per arm). This sample size is also large enough to detect a two point reduction in PUQE-24 score 1 week after randomisation (maximum 15 points, SD 3 points) and differences in quality of life, psychopathology and general health questionnaires ≥ 10 %.

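### The primary birth-weight analysis names neither the centre strata nor the baseline predictors, and the non-parametric fallback does not exempt it

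*Protocol article*

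**What the plan says.** In the protocol article, the section Primary outcome measure states: "The primary outcome will be neonatal birth weight". The section Data analysis then gives its method: "Difference in birth weight will be assessed using parametric testing". No model, covariate or stratum is named.

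The next sentence of Data analysis is more specific about secondary outcomes: "PUQE-24 score will be analysed using multivariate regression and repeated measurements ANOVA or mixed models, as will be quality of life assessments". Other secondary outcomes are to be handled similarly, and the paragraph adds a general rule: "For non-normally distributed variables non-parametric equivalents will be used".

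Three other places bear on the point:

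- Allocation, in the text under Fig. 1: "Stratification according to centre is applied". The ratio is 1:1 with blocks of four.
- Data collection: "To evaluate potential HG and birth weight predictors, detailed information on obstetric and medical history, anthropometrics (before and during pregnancy" and further items are recorded on the case report form.
- Eligibility criteria: singleton and multiple pregnancies are both admitted, so plurality can be known as a baseline characteristic.

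The trial is sized on a mean difference: "The sample size is based on a difference in mean birth weight of 200 g (SD 400 g").

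**The concern.** One paragraph names regression for secondary outcomes and only testing for the primary one. Read plainly, birth weight gets a two-group comparison without adjustment.

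That would cost something in two ways. Stratifying by centre balances the arms within centres. If centre is related to birth weight, an analysis that leaves it out gives a standard error that is too large. Leaving out strong baseline predictors also forgoes precision and leaves chance imbalance uncorrected, in a trial that expects about 108 analysed women.

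The fallback raises a separate issue. It refers to variables in general and makes no exception for birth weight. Multiple pregnancies are eligible, and the Background links the condition to prematurity, so a skewed birth-weight distribution is foreseeable. If the fallback applied, the data would choose the primary test. A rank test does not estimate the mean difference in grams on which the trial is sized.

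**Working it through.** **Inputs from the documents.** Difference 200 g, SD 400 g, alpha 0.05, power 0.80, 10% loss, 60 randomised per arm (Sample size). Sidedness is not stated; two-sided is assumed. Analysed per arm: 60 × 0.9 = 54.

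**Assumed.** R², the share of birth-weight variance explained by centre and baseline covariates. The documents give no value, so a range is shown.

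**Step 1: the plan's own figure.** By the normal approximation, n per arm = 2 × (1.960 + 0.842)² × (400/200)² = 62.8, so 63. Allowing for 10% loss, 63/0.9 = 70 per arm, or 140 in total against the stated 120. One-sided, the figures are 50 per arm, then 56 with loss, or 112 in total. Neither reading gives 120.

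**Step 2: unadjusted power.** The standard error of the difference is 400 × √(2/54) = 77.0 g, and 200/77.0 = 2.60. Noncentral-t power with 106 degrees of freedom is 73.1% (normal approximation 73.8%). With no loss at all (60 per arm) it is 77.5%. One-sided at 54 per arm it is about 83%.

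**Step 3: adjusted power at 54 per arm.** The residual SD is 400 × √(1 − R²), put into the same noncentral-t calculation, two-sided:

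| Assumed R² | Residual SD (g) | SE of difference (g) | Power |
|---|---|---|---|
| 0 | 400.0 | 77.0 | 73.1% |
| 0.10 | 379.5 | 73.0 | about 77% |
| 0.16 | 366.6 | 70.5 | 80.2% |
| 0.20 | 357.8 | 68.9 | 82.1% |
| 0.30 | 334.7 | 64.4 | 86.8% |

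Spending 20 further degrees of freedom on centres and covariates lowers these by about 0.2 points or less (at R² = 0.16, from 80.2% to 80.0%). By the normal approximation, 80% is reached at R² = 1 − 54/62.8 = 0.14.

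**Step 4: centre alone.** Suppose centre explains a share r of the variance and the test ignores it. The effective critical value is 1.960/√(1 − r). By the normal approximation at 54 per arm:

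| Assumed r | Actual two-sided alpha | Power, centre ignored | Power, centre in model |
|---|---|---|---|
| 0.02 | 0.048 | 74.0% | 74.7% |
| 0.05 | 0.044 | 74.4% | 76.0% |
| 0.10 | 0.039 | 74.9% | 78.2% |

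Ignoring centre is therefore conservative. Centre alone recovers roughly 1 to 3 points of power and does not reach 80% in this range. Any larger gain must come from prognostic covariates.

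**The case against.** **Parametric testing does not mean unadjusted.** Linear regression with centre is parametric, so the recommended analysis is compatible with the sentence. A reader might infer that the plan rules out adjustment; the text does not say so. The contrast with the PUQE-24 sentence makes an unadjusted test the likelier reading, no more. A condensed article may also leave the covariate list to the full protocol or the SAP, so the absence of a list is not in itself a fault. What remains is that the sentence published for the primary outcome points to the less efficient analysis.

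**An unadjusted test is not wrong.** After 1:1 randomisation it is unbiased, and ignoring centre errs on the safe side. This stands: the issue is efficiency, not validity.

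**The lack of power has another source.** A reader might blame the choice of test for power below 80%. The documents do not support that. The shortfall arises because 120 does not follow from the stated inputs, and on a one-sided reading there is no shortfall at 54 per arm. Adjustment can offset it only if R² is large enough. It is also not stated whether 400 g already allows for multiple pregnancies, which affects what a plurality covariate would gain.

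**The fallback may not cover the primary outcome.** It follows directly after the sentence on other secondary outcomes and can be read as limited to them. Its wording is general, however, so the ambiguity is real. That the primary test is definitely data-dependent would be too strong a claim.

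**The predictors may be incomplete.** They are taken from records and a questionnaire, for the stated purpose of studying predictors. The documents do not say that they will be available for every woman, so missing covariates must be planned for.

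**Conclusion.** The point holds as a nearly free improvement and a needed clarification, not as an error that invalidates the primary analysis. As worded, the plan most naturally describes an unadjusted comparison that uses neither the stratification factor nor the baseline predictors of birth weight.

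Under the plan's own 200 g and 400 g, two-sided and with 54 per arm, adjustment would move power from about 73% to between about 77% and 87% for R² between 0.10 and 0.30. About 0.16 is needed for 80%. The gain depends wholly on the assumed R² and on 400 g being the total SD. The direction of the gain does not depend on sidedness, provided the covariates predict birth weight.

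The scope of the non-parametric fallback is ambiguous. It should be settled because one available reading changes what the primary analysis estimates.

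**What to change.** Before outcome data are seen, replace the primary-analysis sentence with text to this effect:

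- Birth weight is compared by linear regression on arm, centre (random effect, or small centres pooled) and a short, named list of baseline covariates, for example plurality, parity and pre-pregnancy weight or BMI.
- The adjusted mean difference in grams with its 95% CI is the primary result. The unadjusted difference is a sensitivity analysis.
- If each infant is a record, standard errors allow for correlation between siblings.
- No adjustment is made for variables that arise after randomisation, such as gestational age at birth or later maternal weight. The case report form collects measurements from before and during pregnancy together, so this needs saying.
- The non-parametric fallback does not apply to the primary outcome. If residuals are skewed, the same model is kept, with robust or bootstrap confidence intervals.

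The cost is one paragraph, a few degrees of freedom, a rule for missing covariates, and the need to name the covariates now. It needs no new data items and no extra patients. The sample-size calculation needs its own correction; adjustment should not be offered as a substitute without a justified R².

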### Data collection

At the day of randomisation, participants fill out a questionnaire. This questionnaire consists of validated NVP symptom and NVP specific quality of life measures (24-h Pregnancy Unique Quantification of Emesis and nausea score, PUQE-24; Hyperemesis Impact of Symptoms questionnaire, HIS; Nausea and Vomiting in Pregnancy Quality of Life questionnaire, NVPQoL) [7, 19–21], psychopathology (Hospital Anxiety and Depression Scale, HADS; Symptoms CheckList 90, SCL-90) [22–25] and general health related questions (Short Form 36, SF-36; EuroQol 5 Dimensions questionnaire,EQ5D) [26, 27].

Participants fill out additional questionnaires (NVPQoL, HIS, HADS) 1 and 3 weeks after randomisation and record a diary at weekly intervals (PUQE-24, weight, medication use, dietary intake) from randomisation until 20 weeks gestation. If dietary intake has normalised from 15 weeks gestation onwards, this is no longer recorded. Six weeks postpartum (HADS, SF-36, EQ5D) and 12 months postpartum a final questionnaire is filled out (HADS, SF-36, EQ5D, SCL-90). See Table 1.

**Table 1 Tab1:** Time line MOTHER trial

	T0	T1	T2	T3	T4	T5	T6	T7
	*Randomisation*	*+1 week*	*+ 2 weeks*	*+ 3 weeks*	*+ 4 weeks until GA 20 weeks*	*Birth*	*6 weeks post-partum*	*12 months post-partum*
Diary								
PUQE	X	X	X	X	X			
Current weight	X	X	X	X	X			
Medication use	X	X	X	X	X			
Dietary intake	X	X	X	X	X^a^			
Questionnaires								
General health	X							
NVPQoL	X	X		X				
HIS	X	X		X				
HADS	X	X		X			X	X
SF-36	X						X	X
EQ5D		X					X	X
SCL-90	X							X
Biobank material								
Maternal blood	X							
Cord blood						X		
Placental biopsies						X		

*PUQE* pregnancy unique quantification of emesis and nausea score, *NVPQoL* nausea and vomiting in pregnancy quality of life questionnaire, *HIS* hyperemesis impact of symptoms questionnaire, *HADS* hospital anxiety and depression scale, *SF-36* short form 36, *EQ5D* euroQol 5 dimensions questionnaire, *SCL-90* symptoms checklist 90

^a^If dietary intake has normalised from GA 15 weeks onwards, this will be no longer recorded

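### The open choice between repeated-measurements ANOVA and mixed models for PUQE-24 and quality of life includes a branch that, in its classical form, would drop women with missing forms; how the T0 score enters should be fixed too

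*Protocol article*

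**What the plan says.** The Data analysis section opens with "Data will be analysed according to the intention to treat principle". For the repeated scales it then says "PUQE-24 score will be analysed using multivariate regression and repeated measurements ANOVA or mixed models, as will be quality of life assessments". It does not say which method applies to which scale, whether T0 is an outcome occasion or a covariate, which ANOVA term would be the treatment test, or what happens to a woman with a missing form.

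The schedule is in the Data collection section and Table 1. A questionnaire is completed on the day of randomisation (T0). After that, "Participants fill out additional questionnaires (NVPQoL, HIS, HADS) 1 and 3 weeks after randomisation", and HADS is repeated at 6 weeks and 12 months postpartum. NVPQoL and HIS therefore have three occasions and HADS has five. PUQE-24 is recorded in a weekly diary until 20 weeks of gestation, and the eligibility section allows entry from 5+0 to 19+6 weeks.

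The Sample size section plans 60 women per arm with 10% loss. For PUQE-24 it refers to a "two point reduction in PUQE-24 score 1 week after randomisation (maximum 15 points, SD 3 points"). For quality of life it gives only a relative difference of at least 10%, with no SD.

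**The concern.** The two methods joined by the word or treat incomplete data differently. Classical repeated-measurements ANOVA works on a common, complete set of occasions. A likelihood-based mixed model uses whatever forms each woman returned. If the ANOVA is used with forms missing, randomised women leave the analysis for reasons that arise after randomisation. The trial is open label with a feeding tube in one arm, so form completion could differ between arms, and then the comparison could be biased as well as less precise.

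The role of T0 is a second question. T0 precedes treatment, so it carries no treatment effect. If it is one of the outcome levels, a group effect averaged over occasions is diluted. Otherwise the effect has to be found in a group-by-time term with several degrees of freedom. The scales at stake are secondary outcomes, but they carry the trial's evidence on symptoms and quality of life.

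**Working it through.** **1. Fit of the method to the schedule.**
- Diary: entry at 5+0 weeks leaves 15 weeks until 20+0; entry at 19+6 leaves one day. The series is unequal by design, even with perfect compliance. A common ANOVA grid must cut the series short or leave out late entrants.
- Forms: the plan's 10% loss leaves 60 × 0.9 = 54 per arm. If the same women miss everything, 54 remain complete on every scale. If instead 10% were missing independently at each form, T0 included (assumed), complete cases would be 60 × 0.9³ = 43.7, about 44 per arm, for three forms, and 60 × 0.9⁵ = 35.4, about 35 per arm, for HADS. The documents give no rate per form, so 44 to 54 and 35 to 54 are ranges under these two assumptions.

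**2. Power and the role of T0.** The plan states no power for a repeated-measures analysis, so there is no figure to reproduce. Whether 120 follows from the birth-weight inputs is a separate matter; only the 54 per arm is used here.

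Inputs: three occasions (T0, +1, +3 weeks), n = 54 per arm, two-sided 5% (sidedness is not stated; assumed). SD 1, equal correlation ρ between occasions (assumed), no difference at T0 and a constant effect e at both later occasions. The PUQE-24 inputs give e = 2/3 = 0.67; 0.4 and 0.5 are assumed.

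- Group effect with T0 as an occasion: difference 2e/3; SD of the three-occasion mean √((1 + 2ρ)/3). At e = 0.4, ρ = 0.5: 0.267/0.816 = 0.327; t noncentrality 0.327 × √27 = 1.70; power 39%.
- Group-by-time with T0 as an occasion: F noncentrality (n/2)(2e²/3)/(1 − ρ) = 27 × 0.1067/0.5 = 5.76 on 2 and 212 df; power 56%.
- T0 as covariate, mean of the two later scores: residual SD √((1 + ρ)/2 − ρ²) = √0.5 = 0.707; 0.4/0.707 = 0.566; t noncentrality 0.566 × √27 = 2.94; power 83%.

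| Effect (ρ = 0.5, 54 per arm) | Group effect, T0 as occasion | Group-by-time, T0 as occasion | T0 as covariate |
|---|---|---|---|
| 0.4 SD | 39% | 56% | 83% |
| 0.5 SD | 56% | 76% | 95% |
| 0.67 SD | 80% | 95% | 99.8% |

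Sensitivity at 0.4 SD, for ρ from 0.3 to 0.7: group effect 47% down to 34%, group-by-time 42% up to 79%, covariate 79% up to 93%.

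**3. Complete cases only.** At 44 per arm, 0.4 SD and ρ = 0.5, the two tests with T0 as an occasion fall to 33% and 47%. The like-for-like comparison is the covariate analysis on the same 44 per arm, 75%, and not the 83% at 54 per arm.

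**The case against.** Four points on the other side deserve weight.

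- Mixed models are already a named option, and the text nowhere prescribes deletion. A reader might infer that the plan breaks its own intention-to-treat rule. It does not: the conflict arises only if the ANOVA branch is taken in its classical form. This stands, and the point is conditional for that reason.
- The power gap is not ANOVA against mixed model. With complete data, an ANOVA on the two later scores with T0 as covariate reaches the same 83%, and a mixed model with T0 as an ordinary outcome level loses power as the ANOVA does. This also stands. Striking the ANOVA alone would not recover the power; the role of T0 has to be stated as well.
- A reader might conclude that power is roughly halved. That fits the diluted group effect at 0.4 SD (39% against 83%). It does not fit group-by-time at the same effect (56/83, about two thirds), or either test at 0.67 SD, the only standardised effect for a repeated scale that the documents imply.
- Model details are commonly left to an analysis plan, which is not shown. Silence on baseline coding and missing forms is therefore no finding in itself, and nothing here shows that the method would be chosen after results are seen. What remains is that the article does state a choice, and one option in it fits poorly with the stated schedule and analysis principle.

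The diary argument is also limited, because the PUQE-24 secondary outcome is set at one week after randomisation. It applies only where the weekly series is modelled.

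**Conclusion.** The point holds as a conditional weakness in secondary analyses. The permitted ANOVA, in its classical form, would exclude women with any missing form and could not use the diary whole. Under the two assumptions shown, that leaves 44 to 54 of 60 per arm for three forms and 35 to 54 for HADS.

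The loss from using T0 as an outcome occasion runs from about half the power to almost none, depending on the effect, the correlation and the term tested. The documents give no SD, correlation or missing rate for quality of life, so no single figure can be asserted. The birth-weight analysis is not affected. The change is worth making because it removes the conflict at almost no cost, whichever power figure one prefers.

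**What to change.** In the Data analysis section, strike the repeated-measurements ANOVA option. State that PUQE-24, NVPQoL, HIS and HADS are analysed by a likelihood-based linear mixed model on all available post-randomisation forms, with time as a categorical factor, treatment-by-time, and the T0 score as a covariate and not as an outcome level.

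All four scales are already collected at T0, so the cost is one sentence and no new data. The model relies on data being missing at random, which is weaker than what complete-case ANOVA needs. It cannot recover a woman who returned no form after randomisation. Adding gestational age at entry as a covariate, and fitting the +1 and +3 week forms separately from the postpartum forms, are optional.

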### Data safety monitoring committee

Serious Adverse Events (SAEs) are reported to the Data Safety Monitoring Committee (DSMC). The DSMC can decide, if indicated, to terminate the trial prematurely.

### Ethical considerations

This trial has been approved by the ethics committee of the Academic Medical Centre Amsterdam (Reference number MEC AMC 2012_320) and by the boards of management of all participating hospitals. The trial is registered in the Dutch Trial Register, NTR4197, http://www.trialregister.nl*webcite*. Date of registration: October 2^nd^ 2013. The full protocol can also be downloaded from the study website: www.studies-obsgyn.nl/mother.

## Discussion

Since HG is the largest cause of hospital admission in early pregnancy and has major consequences for maternal quality of life, with possible adverse effects on birth outcomes, evidence based treatment options are needed. Optimal treatment should be safe, reduce maternal complaints, duration of hospital stay and minimise adverse effects on offspring health. This trial will provide evidence on these subjects comparing standard care with intravenous rehydration and early enteral tube feeding in addition to standard care.

## Abbreviations

CRF: case report form
EQ5D: euroQol 5 dimensions questionnaire
HADS: hospital anxiety and depression scale
HG: hyperemesis gravidarum
HIS: hyperemesis impact of symptoms questionnaire
NICE: National Institute for Health and Care Excellence
NVP: nausea and vomiting in pregnancy
NVPQoL: nausea and vomiting in pregnancy quality of life questionnaire
PUQE-24: 24-h pregnancy unique quantification of emesis and nausea score
SCL-90: symptoms checklist 90
SF-36: short form 36
